#### Evaluation of the process

The detailed evaluation of the process aims to study the context of the implementation of PEPITES in the school environment by identifying the external factors which might have an impact on the implementation (levers and obstacles) and on its effectiveness (such as: how well the rule forbidding smoking in the school is applied, other tobacco sessions carried out in the control schools, national campaigns, etc.). The aim of this evaluation is to be able, if the results are positive, to transfer these interventions in other secondary schools. If the results are inconclusive, such an analysis might help to explain the reasons.

### Power of the study

The number of pupils that could be included in the trial is around 750 split into 3 groups of the same size: one control group (T), 2 intervention groups: (A) without EGM experimentation and (B) with EGM use in years 3 and 4. We calculated the rate of reduction of increase in the 2 principal outcomes we could detect, with a global risk α of 5%, a risk β of 20% and an intra-cluster correlation coefficient of “starters and regular smokers” at base line of 0,020 (one-sided test).Comparison Control (T) versus Interventions (A + B) at the end of year 2 on the reduction in increase of *“tobacco use initiation*” (where the increase rate in Essonne is around 10% at the end of the 2 first years of secondary school), and considering that the intervention group A + B (N1) will included ±500 pupils and the control group T (N2) ± 250 (N1/N2 = ½), a significant reduction **≥5.5%** could be detected**.**For the «regular smokers» criterion (where the percentage is estimated at 5% in Essonne at the end of year 2 and 10% in year 4), a significant reduction ≥**4%** at the end of year 2 and **≥ 6.5%** at the end of year 4 could be detected .Comparison 2 by 2 of each of the 3 groups (a control group and 2 intervention groups), for the final analysis at the end of year 4, we will be able to demonstrate a significant reduction increase **≥10%** of “starters” (from the present 25% rate) and a reduction **≥8%** of regular smokers (from the present 10% rate) .

Taking into account in the analysis the factors linked to these 2 outcomes and using appropriate multiple regression analysis and multi-level modeling should allow for an increase in power.

In order to reduce loss of power, the number of pupils lost to follow-up (final questionnaire not filled in at the end of year 2 or year 4) will be minimized by actively searching for them if absent at the time of completing the questionnaire or through the organization of catch-up educational workshops whenever possible.

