**Methods:**

“PEPITES” is an interventional research, using a cluster randomized design. It will allow assessing the effectiveness of interventions both in reducing the tobacco initiation rate and the regular smoking rate of secondary school pupils. We will also evaluate the process of the implementation of the study and thus will help to the transferability of the intervention.

A partnership convention was signed between the JDB Foundation and the National Education authority which designated 6 secondary state schools for the PEPITES trial.

The 6 schools were randomly allocated to 3 groups of 2 clusters each: 1 control group, 2 different intervention groups with 2 workshops per year during 4 years; In one of this group the 2 last workshops will be dedicated to measure the loss of taste due to tobacco smoking. In each school, all pupils in year 1 with a signed parental authorization (744 pupils) have been included in the trial. The interventions targets one of the variables of the TPB and the reinforcement of psycho-social competencies. We estimated that we could detect a reduction of increase ≥5.5 and 8**%** respectively in the 2 principal outcomes (risk α of 5%, and β of 80%).

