### Population selection and randomization

A partnership convention was signed between the JDB Foundation and the Essonne National education authority which designated 6 secondary mixed sex state schools for the PEPITES trial as part of their commitment to health education.

After this designation and before randomization, school head teachers were sent detailed information of the study protocol, followed by a visit by study team members. Then a member of the school management was designated to be the key contact for the study investigators.

The randomization process was carried out by a study investigator during a meeting organized at the JDB Foundation where representatives of each secondary school were present.

The 6 schools were allocated to 3 groups of 2 clusters each (Fig. 1):one group of 2 secondary schools with 2 educational workshops per school year; that is 8 interventions per secondary school over the 4 years,one group of 2 secondary schools with 2 educational workshops per school year; that is 8 interventions per secondary school over the 4 years, with one of the workshops dedicated to measure taste with the electrogustometer during the 3rd and 4th years,

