### Study population

In each secondary school, all pupils in year 1 (grade 6) at the time of the survey, with a signed parental authorization form (94% of year 1 pupils), have been included in the PEPITES trial.

Written parental authorization was requested for the whole duration of the trial after sending a letter which outlined the principal objectives of the trial and the intervention undertaken. The pupils could also refuse to participate even if the parents had given their authorization.

At the start of the study in September 2014, the included population was 744 pupils covering 33 classes in the 6 secondary schools and were expected to be followed, during the 4 years of secondary school.

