### Contamination

The possibility, for the control group, to be influenced by the intervention group is unavoidable if the random selection process is carried out on an individual basis, which leads to the pupils in the compared groups spending time and communicating with each other and possibly copying each other, which can reduce the effect of the interventions and thus the possibility of it being identified. Furthermore it would be unethical not to propose actions which aim to improve health to all the pupils of the same class.

To avoid this phenomenon, the cluster randomization design will determine at random the group allocated to each participating school. With this methodology all of the pupils from one school belong to the same group: either intervention, or control. Agreement of schools to participate occurs before randomization which can leave certain schools frustrated if designated as a control group and they may feel aggrieved; consequently they may try to compensate by involving other preventive actions, which may of course incur a major bias to the trial. It is vital that the control schools understand the importance of their “passive” participation and to propose other educational activities which do not interfere with the trial’s objective. The cluster design may also leads to an increase in the variability of the outcomes and consequently a loss of power which must be compensated for by increasing the number of subjects included in the trial.

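### The five detectable reductions, and the two repeated in the abstract, cannot be reproduced from the stated inputs and are too small for a school-randomised design: power at them is about 40-66%, not 80%

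*Protocol article*

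**What the plan says.** The Power of the study section plans for about 750 pupils, "around 750 split into 3 groups of the same size". It takes a global α of 5%, with "a risk β of 20% and an intra-cluster correlation coefficient of" starters and regular smokers "at base line of 0,020 (one-sided test"). From these it states five detectable reductions:

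- Both intervention groups together (A+B, about 500) against control (T, about 250): 5.5 points for initiation at the end of year 2, from a 10% increase; 4 points for regular smoking at year 2, from 5%; 6.5 points for regular smoking at year 4, from 10%.
- Groups compared two by two at year 4: 10 points for starters, from 25%; 8 points for regular smokers, from 10%.

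The abstract carries two of these forward: "We estimated that we could detect a reduction of increase ≥5.5 and 8"%.

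The cluster is named under Population selection and randomization: "The 6 schools were allocated to 3 groups of 2 clusters each". Under Study population, "the included population was 744 pupils covering 33 classes in the 6 secondary schools". The power section gives no cluster size and no design effect.

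**The concern.** Whole schools were randomised, and they are large. Even a small intra-cluster correlation then inflates the variance several-fold, so 250 pupils in two schools carry far less information than 250 pupils randomised one by one. The stated reductions look too small to have absorbed that inflation.

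There is also a sign of inconsistency that depends on no method. Initiation at year 2 and regular smoking at year 4 (A+B against T) have the same 10% control rate, the same group sizes and the same stated correlation and error rates, yet one detectable reduction is 5.5 and the other 6.5. One calculation cannot give both.

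At stake is the sensitivity claimed for both principal outcomes. Under Outcomes measures these are initiation (A+B against T, at years 2 and 4) and regular smoking at year 4 (groups two by two). The abstract's 5.5 and 8 belong to them.

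**Working it through.** **Inputs.** One-sided α 5% (z = 1.645), power 80% (z = 0.842), correlation ρ = 0.020, control rates and group sizes: Power of the study. Cluster = school, two per group: Population selection and randomization. School size: 744/6 = 124 enrolled, or 750/6 = 125 planned. I read the reductions as absolute percentage points; as relative reductions they would be smaller still (5.5% of 10% is 0.55 points). I assume no dropout and no gain from covariates, because the article quantifies neither.

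**Design effect.** DE = 1 + (125 − 1) × 0.020 = 3.48 (3.46 with 124). Effective sizes are 250/3.48 = 71.8 per group and 500/3.48 = 143.7 for A+B.

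**Trying to reproduce the stated figures** (reductions detectable at 80% power, in points, pooled variance):

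| Comparison | Stated | No clustering, one-sided 5% | No clustering, two-sided 5% | Class as cluster, one-sided 5% | DE implied by the stated figure, one-sided 5% |
|---|---|---|---|---|---|
| Initiation Y2, A+B v T | 5.5 | 5.0 | 5.48 | 5.8 | 1.27 |
| Regular Y2, A+B v T | 4 | 3.4 | 3.6 | 3.8 | 1.62 |
| Regular Y4, A+B v T | 6.5 | 5.0 | 5.48 | 5.8 | 1.92 |
| Starters Y4, pairwise | 10 | 9.0 | 10.00 | 10.6 | 1.27 |
| Regular Y4, pairwise | 8 | 5.7 | 6.3 | 6.6 | 2.32 |

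Class as cluster uses 744/33 = 22.5 pupils, so DE = 1 + 21.5 × 0.02 = 1.43. With unpooled variance that column is 6.2, 4.3, 6.2, 10.5 and 6.6. No column matches all five figures. The 5.5 and the 10 coincide with unclustered two-sided tests. The implied design effects differ from one another, and all lie below 3.48.

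**Power at the stated reductions with DE = 3.48.** Unpooled: power = Φ(d/SE − 1.645), with SE = √(p₁q₁/n₁ + p₂q₂/n₂) on effective sizes.

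- Initiation Y2: SE = √(0.10 × 0.90/71.8 + 0.045 × 0.955/143.7) = 0.0394; 0.055/0.0394 = 1.396; Φ(−0.249) = 40%.
- Regular Y4, pairwise: SE = √((0.10 × 0.90 + 0.02 × 0.98)/71.8) = 0.0391; 0.08/0.0391 = 2.048; Φ(0.403) = 66%.

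The pooled version puts the common rate in the null standard error. The t version refers d/SE to a noncentral t with (schools − 2) degrees of freedom: 4 for A+B v T and 2 for pairs. The detectable reduction is the d at which power equals 80%.

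| Comparison | Stated | Power at stated, unpooled / pooled | Power at stated, school-level t | Detectable at 80%, unpooled / pooled |
|---|---|---|---|---|
| Initiation Y2, A+B v T | 5.5 | 40% / 47% | 31% | 9.0 / 8.1 |
| Regular Y2, A+B v T | 4 | 43% / 56% | 34% | none: 62% / 78% even at a zero rate |
| Regular Y4, A+B v T | 6.5 | 52% / 60% | 40% | 9.0 / 8.1 |
| Starters Y4, pairwise | 10 | 45% / 44% | 27% | 15.4 / 15.6 |
| Regular Y4, pairwise | 8 | 66% / 65% | 39% | 9.2 / 9.3 |

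**Sensitivity to the correlation.** To give 80% power at the stated figures (unpooled), the school-level correlation would have to be 0.0008, 0.0019, 0.0048, 0.0023 and 0.011 in the order of the table, against the stated 0.020. At an assumed 0.01, initiation at year 2 is detectable at 7.5 points (unpooled). At 0.03 it is 9.0 pooled and out of reach unpooled.

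**The case against.** The best defence is that the section names no cluster level, speaks of a global α, and expects covariate adjustment and multi-level modelling to raise power. All five figures exceed what an unclustered one-sided 5% test would give, so some allowance for clustering, multiplicity or rounding may be in them. The correlation is also a baseline value; for change within pupils, with matched data, it could be lower.

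Part of this stands. A reader might infer that clustering was ignored altogether. The documents do not support that: only two of the five figures match an unclustered calculation, and only with a two-sided test where the plan says one-sided. How the other three arose cannot be determined. Nor is 27% the plan's power. It comes from a 2-df t test that the article does not specify; its Statistical analysis section speaks of logistic models that take account of the cluster effect.

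The rest does not rescue the figures. The article makes the school the cluster, and class-level clustering does not reproduce the set. The gain from modelling is unquantified and is presented as additional to the stated figures. This is also more than the brevity of an article, because the inputs and results are both printed and they disagree.

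Two further inferences should be resisted. Regular smoking at year 2 is underpowered, not untestable, and the principal analysis of that outcome is at year 4. The Contamination section's remark that clustering brings "consequently a loss of power which must be compensated for by increasing the number of subjects included in the trial" is a general comment on cluster designs. Adding schools also adds subjects, so it is not an error.

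**Conclusion.** The point holds. From the plan's own inputs, none of the five stated reductions carries the school-level design effect of 3.48, and power at them is about 40-66% by normal approximation rather than 80%. With school-level t critical values it is about 27-40%; that range belongs to a different and stricter method and should be reported as such. The gap is not uniform. It is large for initiation at year 2 (8.1-9.0 against 5.5) and for starters pairwise (about 15.5 against 10), though the latter is not one of the principal comparisons. It is modest for regular smoking pairwise (9.2-9.3 against 8).

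This rests on schools of equal size, a correlation of 0.020 that persists to follow-up, no dropout and no covariate gain. Dropout would lower power slightly. Adjustment or a lower correlation for change could raise it by an amount the article does not give. A reader might infer that a null result will be taken to exclude a 5.5- or 8-point effect. The article does not say so, and its process evaluation allows for inconclusive results; but the stated sensitivity would invite that reading.

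**What to change.** Recompute all five detectable reductions with the school as the cluster, and restate them in the power section together with the abstract's 5.5 and 8. State the cluster size, the design effect, the sidedness and the variance formula, so that a reader can reproduce each figure and the 5.5/6.5 discrepancy disappears. Preferably use small-sample critical values based on the number of schools, and show a range of intra-cluster correlations, for example 0.01 to 0.05, labelled as an assumption. An estimate from the trial's own six schools would be too imprecise to replace that range. Say that, at a correlation of 0.020, regular smoking at year 2 is underpowered for any reduction.

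The cost is a recalculation and a few sentences. No schools or pupils are added, and the Contamination section can stay as it is. The price is a less favourable statement of what the trial can detect.

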### Proposed educational interventions

The proposed interventions targets one of the variables of the TPB (i.e., attitude, subjective and social norms, perceived control and intention) and the reinforcement of psycho-social competencies (resistance to pressure, critical mind, reasoned choice, civil responsibility). Teaching methods are based on inter-activity and practical experimentation.➢ The educational sessions are adapted to the age of the pupils, tested and conducted by prevention professionals from the JDB Foundation. They are carried out during school time and last 45 min. In chronological order they cover the following themes: reasons for starting smoking, awareness of the risks taken, explanation of the marketing strategies of the tobacco industry, the mechanism of addiction and the effects on health (Table 1).➢ Experimental session measuring taste change linked to tobacco use. Our hypothesis is that the concrete consciousness of the harm caused by tobacco use could increase children awareness regarding the harmful effects of tobacco and consequently improve their motivation to not start smoking or to stop if they have started. A tool, the electrogustometer (Fig. 2), makes it possible to measure the taste sensitivity of the tongue - sensitivity which reduces significantly for a smoker from the first cigarette regularly smoked [17].

**Table 1 Tab1:** Content of educational sessions

Year 1 (Age ± 11): Why do people start smoking?	
ᅟThink about the reasons for starting smoking and be aware of the space tobacco occupies in our society today (Peer pressure).	
ᅟAt the end of the workshop, the pupils should be able to: ᅟᅟ− Think about what influences a person to start smoking (or not) ᅟᅟ− Expose the major lines of the history of tobacco in our society	
Year 2 (Age ± 12): Risk behavior, Stress management, Risk taking and alternatives	
ᅟThink about what risks they take in their daily lives	
ᅟAt the end of the workshop, the pupils should be able to: ᅟᅟ− Explain what constitutes risk behavior ᅟᅟ− Imagine alternatives to risk taking	
Year 3 (Age ± 13): Manipulation by the tobacco industry – Marketing strategy	
ᅟDevelop a critical mind by analyzing sales techniques and influencing techniques of the tobacco industry	
ᅟAt the end of the workshop, the pupils should be able to: ᅟᅟ• Discuss the main determinants in the regular consumption of tobacco ᅟᅟ• Quote the marketing strategies used by the tobacco industry	

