### Outcomes measures

#### Evaluation of the results

The 2 principal outcomes for the PEPITES trial are:The prevalence of pupils having experimented (at least once) tobacco smoking at the end of year 2 and year 4 as compared to beginning of year 1 (comparison of the 2 intervention groups together versus the control group)The prevalence of regular (at least weekly) cigarette smokers at the end of year 4 (comparisons of the 3 groups 2 by 2).These outcomes will be collected at the beginning of each year and at the end of year 2 and 4, and their evolution over time analyzed in each of the groups and compared. Outcomes prevalence measures are only based on pupils declaration.The secondary outcomes include experimentation with hookah, cannabis, electronic cigarettes, perception of norms, attitudes and future intentions of the participants with regard to smoking.

The various determinants which may have a role in starting smoking or becoming a regular smoker (gender, siblings, sporting activity, home area (ZUS), smokers in the entourage (parents, friends…) will also be studied and reported.

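### Year-2 and year-4 detectable reductions rest on a single baseline ICC of 0.020 with no range, and the printed reductions do not reach 80% power at that value or above

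*Protocol article*

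**What the plan says.** All inputs are in the protocol article.

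- *Power of the study* sets the error rates "with a global risk α of 5%, a risk β of 20" per cent and one ICC: "an intra-cluster correlation coefficient of “starters and regular smokers” at base line of 0,020 (one-sided test". No other ICC appears anywhere in the article.
- The same section plans a total as follows: "The number of pupils that could be included in the trial is around 750 split into 3 groups of the same size". For the pooled comparison, the intervention groups "will included ±500 pupils and the control group T (N2) ± 250 (N1/N2 = ½".
- *Population selection and randomization*: "The 6 schools were allocated to 3 groups of 2 clusters each". The school is therefore the cluster, with about 750/6 = 125 pupils each.
- Baseline is entry to year 1. The content table in *Proposed educational interventions* dates this: "Year 1 (Age ± 11): Why do people start smoking".
- *Evaluation of the results* sets the principal outcomes later: experimentation at the end of years 2 and 4, and "The prevalence of regular (at least weekly) cigarette smokers at the end of year 4 (comparisons of the 3 groups 2 by 2".
- For regular smoking the power section gives reference rates, "where the percentage is estimated at 5% in Essonne at the end of year 2 and 10% in year 4". For starters in the year-4 pairwise comparison it gives a present rate of 25%.
- The printed detectable reductions for A+B against T are 5.5 (initiation, year 2), 4 (regular smoking, year 2) and 6.5 (regular smoking, year 4). For the year-4 pairwise comparisons they are 10 (starters) and 8 (regular smokers). The abstract repeats 5.5 and 8.

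**The concern.** The ICC belongs to a different time point from every outcome it supports, and one value stands for two outcomes of different frequency. The ICC of a binary outcome need not stay fixed as prevalence changes, and the plan's own rates change a good deal: regular smoking doubles from 5% to 10% between years 2 and 4.

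With only two schools per group and about 125 pupils in each, the ICC is the input that matters most. If the follow-up ICC differs from 0.020, the detectable reductions move substantially. A reader of an inconclusive result, which *Evaluation of the process* foresees, would rely on those reductions to judge what the trial could have shown.

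**Working it through.** **Inputs.** One-sided 5%; 250 pupils in T and in each single arm, 500 in A+B; 125 per school; reductions read as absolute percentage points; equal clusters and no loss to follow-up (assumed).

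**Formulas.** Design effect DEFF = 1 + (125 − 1) × ICC, which is 3.48 at 0.020, 2.24 at 0.01 and 5.34 at 0.035.
Power = Φ[(δ − 1.645 × SE0)/SE1], with SE0² = DEFF × p̄(1 − p̄)(1/n0 + 1/n1) and SE1² = DEFF × [p0(1 − p0)/n0 + p1(1 − p1)/n1]. The unpooled variant replaces SE0 by SE1.

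**Step 1: the plan's figures.** Detectable reductions at 80% power, in the order initiation year 2, regular year 2, regular year 4 (pooled groups), starters year 4, regular year 4 (pairwise):
- printed: 5.5, 4, 6.5, 10, 8
- no clustering: 5.0, 3.4, 5.0, 9.0, 5.7
- classes as clusters (744/33 = 22.5 pupils, DEFF 1.43): 5.8, 3.8, 5.8, 10.6, 6.6
- schools as clusters (DEFF 3.48): 8.1, not reachable from 5%, 8.1, 15.5, 9.3

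No variant gives all five printed values.

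**Step 2: one case by hand.** Starters 25% to 15%, ICC 0.020: p̄ = 0.20; SE0 = √(3.48 × 0.16 × 2/250) = 0.0667; SE1 = √(3.48 × (0.1875 + 0.1275)/250) = 0.0662; (0.10 − 1.645 × 0.0667)/0.0662 = −0.15; power 44%.

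**Step 3: sensitivity to the ICC** (pooled null variance; last column pooled / unpooled).

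| Printed effect | ICC 0.01 | ICC 0.02 | ICC 0.035 | ICC giving 80% |
|---|---|---|---|---|
| Initiation yr 2, 10% to 4.5%, A+B v T | 61% | 47% | 37% | 0.0022 / 0.0008 |
| Regular yr 2, 5% to 1%, A+B v T | 70% | 56% | 45% | 0.0050 / 0.0019 |
| Regular yr 4, 10% to 3.5%, A+B v T | 75% | 60% | 47% | 0.0075 / 0.0048 |
| Starters yr 4, 25% to 15%, pairwise | 59% | 44% | 33% | 0.0022 / 0.0023 |
| Regular yr 4, 10% to 2%, pairwise | 81% | 65% | 49% | 0.0106 / 0.0110 |

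The unpooled formula gives 66% and 50% in the last row at 0.02 and 0.035, and 52% and 39% for 10% to 3.5%. These are normal approximations. A t reference with 4 or 2 degrees of freedom (6 or 4 schools) lowers the ICC 0.02 column to 32%, 34%, 40%, 27% and 40%.

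**Step 4: what a follow-up ICC might be (assumption, not in the article).** Take a normal school effect on the log-odds scale with constant SD, solved so that the ICC is 0.020 at the baseline prevalence.
- Regular smoking, baseline 5% (the year-2 rate, so probably a ceiling): SD 0.62, ICC 0.035 at 10%.
- Starters, baseline 15% (25% less the 10-point rise over two years): SD 0.40, ICC 0.028 at 25%. With baseline 5% instead: ICC 0.065.

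At ICC 0.028, power for 25% to 15% is 37% (38% unpooled) and the detectable reduction is about 17 points.

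**The case against.** A reader might infer that the year-4 ICC must exceed 0.020, so that the baseline value in itself overstates power. The article does not support that.

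- It gives no follow-up ICC and does not say that the ICC rises. The values in step 4 come wholly from the constant log-odds SD. At ICC 0.01 power is higher than at 0.020.
- A constant ICC is not a constant between-school variance. That variance is ICC × p(1 − p), which at 0.020 already goes from 0.00095 at 5% to 0.0018 at 10% and 0.00375 at 25%.
- The plan speaks of a reduction in increase, compares experimentation with the start of year 1, and foresees matched data and adjustment. Stable school differences partly cancel in such an analysis, so the relevant ICC could be below 0.020.
- It cannot be confirmed that 0.020 was applied unchanged. Initiation at year 2 and regular smoking at year 4 share a 10% rate and 500 against 250 pupils, yet show 5.5 and 6.5, so some unstated input differs.
- The 25% for starters can be read as an increase rather than a prevalence; the 15% baseline ceiling then fails.
- It would also be too strong to say that at ICC 0.035 no reduction from 10% reaches 80% power. That holds with unpooled variance (74% for 10% to 0%) and pairwise (72% with pooled null variance), but A+B against T with pooled null variance reaches 86%.

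All of this stands against a claim of direction. It does not remove the mismatch of time point, the absence of a range, or the shortfall at 0.020 itself. A source for the ICC may well sit in the full protocol, but the detectable reductions are stated in this article and are what readers will use.

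**Conclusion.** The point holds in limited form. The only ICC stated is a baseline value for two outcomes jointly, and it supports year-2 and year-4 reductions. Whether the follow-up ICC is higher or lower is not established by the article.

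What can be shown is how much depends on it. Pairwise power for year-4 regular smoking runs from about 81% to 50% as the ICC goes from 0.01 to 0.035, and for starters from about 59% to 33%. The printed reductions reach 80% power only at an ICC between roughly 0.001 and 0.011, depending on comparison and variance formula, so they are not met at the plan's own 0.020 or at anything higher. That shortfall arises because the printed figures do not carry the school design effect of 3.48; it does not prove that the baseline ICC is too low.

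The result assumes absolute reductions, equal schools of 125, no loss to follow-up and a normal approximation; the last two favour the plan.

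**What to change.** In *Power of the study* and in the abstract, restate the detectable reductions separately for experimentation (end of year 2, end of year 4) and regular smoking (end of year 4; also end of year 2 if that figure is kept). Use the school design effect over an ICC range on both sides of 0.020, for example 0.01 to 0.065. Label 0.020 as a baseline value and every follow-up value, higher or lower, as an assumption.

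The cost is one recalculation and some rewording, with no new schools, pupils or data. The downside is less favourable figures: for year-4 starters at ICC 0.020, about 15.5 points instead of 10, and about 12.9 even at 0.01.

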### Data collection

The procedures and tools for data collection were created by the JDB Foundation team and were tested before the implementation of the trial in various secondary schools not included in the study.

Regarding the process, qualitative methods (semi-directive interviews and completion of a log-book notifying absences, refusals, computers problem as well as comments relating to the data collection) were put in place.

Questionnaires were used to identify reasons for parents’ refusals and to collect the opinions of the main participants (teaching staff, management team).

Regarding the pupils whose parents had given their authorization and who agreed to participate, the answers to the questions were collected by means of computerized and anonymous self-assessment questionnaires (Table 2), completed in class during school time. The conditions for completion of the questionnaire were to be alone at the computer under the supervision of two adults per class to avoid any copying or minimize reporting bias and to help if necessary.

**Table 2 Tab2:** Guarantee of anonymity

The self-assessment questionnaire contains a code which allows the answers from the same pupil to be followed from year to year. This numbered code was randomly generated and assigned to each pupil in the trial. The code is recorded in a list with the pupils’ names which is held by the headmaster of the school in his role as a reliable third party: the headmaster does not have access to the pupils’ answers; the JDB Foundation team which performs the analysis does not have access to the list of pupils’ names. Each time a new questionnaire is completed the code is again supplied to the pupil thanks to the paper list held by the headmaster of the school. This information is also included in the information letter to parents and pupils before completion. The procedures put in place have met that the National Commission for Data Protection and Liberties (CNIL -France) requirements and has authorized the implementation of the PEPITES trial.	

The pupils were clearly informed that neither the teachers, nor their parents, nor anybody else could match their name to their answers. Pupils were also informed that they had the right to refuse to take part.

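### The year-2 initiation figure of 5.5 points is calculated on full enrolment with no stated allowance for the loss to follow-up that the same section expects

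*Protocol article*

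**What the plan says.** All references are to the Protocol article.

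- **Power of the study** starts from the whole pool of pupils: "The number of pupils that could be included in the trial is around 750 split into 3 groups of the same size". For initiation at the end of year 2 it takes a control increase of about 10% and gives the group sizes: "considering that the intervention group A + B (N1) will included ±500 pupils and the control group T (N2) ± 250". It concludes that a reduction of 5.5 or more is detectable. The abstract repeats 5.5.
- The same section prints four further detectable reductions: 4 and 6.5 for regular smoking at years 2 and 4 (control against both intervention groups), and 10 for starters and 8 for regular smokers in the year-4 pairwise comparisons. Group sizes are not restated for these.
- **Study population** gives the number actually enrolled in September 2014: "the included population was 744 pupils covering 33 classes in the 6 secondary schools".
- **Power of the study** then turns to loss: "In order to reduce loss of power, the number of pupils lost to follow-up (final questionnaire not filled in at the end of year 2". The definition covers the year-4 questionnaire too, and such loss is to be kept small by seeking absent pupils and by catch-up workshops. No loss rate and no evaluable number are given.
- **Statistical analysis** plans to report how many pupils were lost.

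**The concern.** A detectable reduction at the end of year 2 should rest on the pupils who will have an end-of-year-2 questionnaire. The article uses the number who entered. It names loss as something that reduces power and then prints a figure from which no loss has been taken.

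Initiation is one of the two principal outcomes, and its 5.5 is one of the two figures carried into the abstract. If the result is null, readers will use that figure to judge what the trial could have ruled out. If it is too favourable, they will draw too firm a conclusion.

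**Working it through.** **Inputs, all from Power of the study unless noted**
- Control 250, both interventions 500 (ratio 2); pairwise 250 against 250.
- One-sided 5%, power 80%, intra-cluster correlation 0.020. The cluster size used is not stated.
- Control rates: 10% (initiation, year 2), 5% and 10% (regular smoking, years 2 and 4), 25% (starters, year 4).
- 744 pupils in 33 classes: 744/33 = 22.5 per class (Study population). Two schools per group: 250/2 = 125 per school.
- Loss: no rate in the article, so 10%, 20% and 30% are assumptions.
- The printed reductions are read as percentage points.

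**Formulae**
- Design effect: DE = 1 + (m − 1) × 0.020, with m pupils per cluster.
- Loss L multiplies both the group size and m by (1 − L). Effective size = group size × (1 − L) / DE.
- Power = Φ((d − 1.645 × s0) / s1). Here s0 is the pooled standard error, s1 the unpooled one, and d the difference. The detectable reduction is the d that gives 80%.
- The full 5% is used for every comparison and no correction is made for the small number of schools. Both choices favour the plan.

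**Attempt to reproduce the printed figures (full enrolment)**

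| Figure | Printed | No DE | Class DE 1.43 | School DE 3.48 |
|---|---|---|---|---|
| Initiation, year 2 | 5.5 | 4.98 | 5.77 | 8.11 |
| Regular, year 2 | 4 | 3.35 | 3.83 | not attainable |
| Regular, year 4 | 6.5 | 4.98 | 5.77 | 8.11 |
| Starters, pairwise, year 4 | 10 | 8.96 | 10.55 | 15.55 |
| Regular, pairwise, year 4 | 8 | 5.72 | 6.62 | 9.28 |

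No single variant gives all five. The 5.5 and the 10 are matched at full enrolment by a two-sided 5% test with no design effect (5.48 and 10.00), which is not what the section states.

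**Worked example: initiation at year 2, class-level clustering**

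*No loss.* DE = 1 + 21.5 × 0.020 = 1.43. Effective sizes are 250/1.43 = 174.8 and 500/1.43 = 349.7. With p1 = 0.10 and p2 = 0.045, the pooled rate is (0.10 + 2 × 0.045)/3 = 0.0633, s0 = 0.02256 and s1 = 0.02525. Power = Φ((0.055 − 1.645 × 0.02256)/0.02525) = Φ(0.71) = 76%.

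*20% loss.* m = 18 and DE = 1.34, so the effective control size is 200/1.34 = 149.3. Then s0 = 0.02442 and s1 = 0.02733. Power = Φ((0.055 − 1.645 × 0.02442)/0.02733) = Φ(0.54) = 71%.

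The 5.5 needs an effective control size of 197. Full enrolment supplies about 175.

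**Detectable reduction by assumed loss, class-level clustering**

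| Figure (printed) | 0% | 10% | 20% | 30% |
|---|---|---|---|---|
| Initiation, year 2 (5.5) | 5.77 | 5.95 | 6.15 | 6.40 |
| Power at 5.5 | 76% | 74% | 71% | 67% |
| Starters, pairwise, year 4 (10) | 10.55 | 10.91 | 11.33 | 11.84 |
| Power at 10 | 76% | 73% | 70% | 66% |
| Regular, year 2 (4) | 3.83 | 3.93 | 4.05 | 4.19 |
| Regular, year 4 (6.5) | 5.77 | 5.95 | 6.15 | 6.40 |
| Regular, pairwise, year 4 (8) | 6.62 | 6.82 | 7.06 | 7.34 |

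The 4 points fails from about 16% loss. The 6.5 and the 8 hold to about 33% and 47%.

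**School-level clustering.** At 20% loss, m = 100, DE = 2.98, and initiation moves from 8.11 to 8.30 points. Pairwise starters move from 15.55 to 16.00.

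**The case against.** **A loss allowance may be hidden in the figures.** With no design effect and a one-sided 5% test, 20% loss gives 5.46 points for initiation and 9.93 for pairwise starters, close to the printed 5.5 and 10. This is arithmetically possible. It would mean, however, that the stated intra-cluster correlation was not used, and the section prints 500 and 250 rather than reduced numbers. That a reader cannot tell is a reason to print the evaluable number.

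**Loss is a small matter beside clustering.** This stands. With class-level clustering 20% loss adds about 0.4 points (6.15 − 5.77), and at school level, the unit randomised, about 0.2 (8.30 − 8.11). The level at which the correlation is applied matters far more.

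**Enrolment is closed, loss is handled in words, and the article is a condensed text.** Also true, and nothing here calls for more pupils. But the article prints the inputs and the result of this calculation, so the printed figure can be judged as it stands.

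**Three stronger readings are tempting and not supported.**
- *All five figures assume zero loss.* Group sizes are printed only for year-2 initiation, and the year-4 regular-smoking figures exceed the zero-loss values at class level.
- *Year-4 regular smoking suffers most.* On the class-level basis it has the most room for loss.
- *Pupils who leave the six schools cannot be followed.* Data collection says that questionnaires are completed in class and that each headmaster keeps the list of link codes. The article says nothing about pupils who change school, so this would be inference from silence.

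**Conclusion.** The point holds for the year-2 initiation figure. The 5.5 points rests on full enrolment with no stated deduction, while the same section expects loss and says that it costs power. With the stated correlation applied at class level, power at 5.5 is already 76% with everyone followed, so the figure holds no reserve. At 20% loss power is 71% and the detectable reduction is 6.15 points. The pairwise 10 points for starters is in the same position by recalculation, although its group sizes are not restated. The year-2 4 points for regular smoking has a reserve of about 16% only. No such claim is made for the 6.5 and the 8.

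These sizes depend on the assumed loss rates, on class-level clustering and on a pooled normal-approximation test. With school-level clustering all five figures fail before any loss, and loss changes little further. The defect is a power statement more favourable than its own inputs support; it does not invalidate the design or the analysis.

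**What to change.** In Power of the study:

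1. State the number of pupils assumed to have a questionnaire at the end of year 2 and at the end of year 4, for each comparison.
2. Recompute all five detectable reductions at those numbers. Use the loss observed up to the end-of-year-2 questionnaire if it is known; otherwise show 10%, 20% and 30% and label them as assumptions.
3. Do this together with the design effect, and state the cluster size used. Correcting for loss alone would leave the larger problem in place.
4. Label the current 5.5 as resting on full enrolment, and update the 5.5 in the abstract.

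The cost is recalculation and wording. No pupils, visits or analyses are added. On the bases shown here, the initiation and pairwise starters figures become less favourable.
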